## Abstract

**Background:**

Although life-saving in selected patients, ECMO treatment still has high mortality which for a large part is due to treatment-related complications. A feared complication is ischemic stroke for which heparin is routinely administered for which the dosage is usually guided by activated partial thromboplastin time (aPTT).

However, there is no relation between aPTT and the rare occurrence of ischemic stroke (1.2%), but there is a relation with the much more frequent occurrence of bleeding complications (55%) and blood transfusion. Both are strongly related to outcome.

**Methods:**

We will conduct a three-arm non-inferiority randomized controlled trial, in adult patients treated with ECMO. Participants will be randomized between heparin administration with a target of 2–2.5 times baseline aPTT, 1.5–2 times baseline aPTT, or low molecular weight heparin guided by weight and renal function. Apart from anticoagulation targets, treatment will be according to standard care. The primary outcome parameter is a combined endpoint consisting of major bleeding including hemorrhagic stroke, severe thromboembolic complications including ischemic stroke, and mortality at 6 months.

**Discussion:**

We hypothesize that with lower anticoagulation targets or anticoagulation with LMWH during ECMO therapy, patients will have fewer hemorrhagic complications without an increase in thromboembolic complication or a negative effect on their outcome. If our hypothesis is confirmed, this study could lead to a change in anticoagulation protocols and a better outcome for patients treated with ECMO.

**Trial registration:**

ClinicalTrials.gov NCT04536272. Registered on 2 September 2020. Netherlands Trial Register NL7969

## Administrative information

Note: the numbers in curly brackets in this protocol refer to SPIRIT checklist item numbers. The order of the items has been modified to group similar items (see http://www.equator-network.org/reporting-guidelines/spirit-2013-statement-defining-standard-protocol-items-for-clinical-trials/).

Role of sponsor {5c}	The UMCG government will have no role in the design of the study and collection, analysis, and interpretation of data and writing the manuscript.

## Introduction

### Background and rationale {6a}

Extracorporeal life support (ECLS) through extracorporeal membrane oxygenation (ECMO) utilization can support the heart and lung for an extended period, up to months, and is deployed in the intensive care unit (ICU) [1]. ECMO seems an efficient therapy in terms of survival benefit, but mortality is still high [2]. This is in part due to the condition that necessitates ECMO, but there is also significant treatment-related mortality. Exposure of blood to the nonbiologic surfaces of an extracorporeal circuit initiates a complex inflammatory response involving both the coagulation and the inflammatory response pathway. A feared complication is a thromboembolic stroke due to clotting related to the ECMO system. To prevent this, and to preserve ECMO circuit patency, patients are treated with systemic anticoagulation, usually with unfractionated heparin (UFH) of which the dosage is guided by activated partial thromboplastin time (aPTT) target of 2.0–2.5 times baseline (approximately 60–75 s). This target is adapted from other diseases or indications for therapeutic anticoagulation and not validated. In recent years ECMO equipment has been improved, e.g., heparin-coated cannulas, but anticoagulation targets remained unchanged [2]. More importantly, there seems to be no relationship between the level of anticoagulation and the occurrence of a thromboembolic stroke. In contrast, there is however a strong relationship between the level of anticoagulation and the occurrence of bleeding complications as well as the need for a blood transfusion which is directly related to poor outcome. Moreover, fatal hemorrhagic stroke is far more frequent than fatal thromboembolic stroke [1, 3]. Taken together, one might postulate that intensive heparin treatment, in this case, might lead to more problems than benefits. However, there is a paucity of studies evaluating different anticoagulation strategies in patients supported with ECMO and no randomized trials are comparing one strategy to another [4–7]. A comprehensive guideline for the use and monitoring of anticoagulation during ECMO therapy may be found on the Extracorporeal Life Support Organization (ELSO) website [8]. This guideline stops short of any mandate, given the lack of evidence in favor of most of the practices reviewed. Rigorous evaluations of anticoagulation use in ECMO patients are therefore urgently needed.

## Objectives {7}

Our primary research question is if anticoagulation with UFH with reduced anticoagulation targets or anticoagulation with low molecular weight heparin (LMWH) leads to a reduction in the occurrence of major bleeding without an increase in thromboembolic complications or a negative effect on outcome compared to the standard practice of high anticoagulation targets with UFH. We expect fewer complications and improvement of survival after ECMO therapy for both interventions.

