## Trial design {8}

We will perform a multi-center phase 3, three-armed, randomized, non-inferiority open-label study in patients receiving veno-venous (VV) and veno-arterial (VA) ECMO therapy. Allocation is in a 1:1:1 ratio.

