### Outcomes {12}

The primary outcome parameter of this study is a composite endpoint consisting of (1) severe hemorrhagic complications according to the ELSO definitions: clinically overt bleeding with a transfusion requirement of more than 20 ml/kg red blood cell (RBC) transfusions or >3U RBC in one calendar day. Bleeding that is retroperitoneal or pulmonary or involves the central nervous system or bleeding that requires surgical intervention will also be considered major bleeding; (2) severe thromboembolic complication defined as ischemic stroke, limb ischemia, or acute pump failure; (3) mortality at 6 months. This composite outcome was designed to capture the net clinical effect of reduced anticoagulation targets, e.g., a reduction of major bleeding not counteracted by an increase in thromboembolic complications. Mortality is part of the composite outcome to capture unknown or unmeasured effects of reduced anticoagulation.

Secondary endpoints are all other variables that may be affected by the anticoagulation regime: (1) blood transfusions, (2) quality of life (HR-QoL) at 6 months, (3) exchange of the membrane oxygenator, (4) vessel thrombosis after ECMO removal detected by echography, (5) pulmonary embolism, (6) costs, (7) the individual components of the composite outcome, (8) all thromboembolic complications combined, and (9) all hemorrhagic complications combined.

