## Statistical methods

### Statistical methods for primary and secondary outcomes {20a}

#### Primary study parameters

The primary analysis will be a single comparison between the treatment groups of the primary outcome measure after 6 months. This analysis will be performed according to the intention-to-treat principle. To assess the effect of treatment with lower anticoagulation targets or LMWH with standard care, an absolute risk reduction of poor outcome and its corresponding 95% confidence interval will be calculated. The confidence interval of the risk reduction will be compared with the non-inferiority marge of 7.5% of both intervention arms adjusted for center and ECMO mode.

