### Dissemination plans {31a}

If our study indeed shows that reduced anticoagulation targets improve outcomes, the next steps will be to disseminate the obtained insights among health care professionals, patients, and policy makers and to implement reduced anticoagulation targets in clinical practice.

Successful implementation starts with involving the various stakeholders from the start. In our study, it is especially relevant to involve both referrers, other professionals (health technology assessment and implementation experts), and patients, and therefore, we included them in our project group. The project group members have a broad network in the Netherlands, are members of the Dutch Society of Intensive Care (NVIC) and represented in the commission ECLS of the NVIC and European Society of Intensive Care Medicine (ESICM), have written the current Dutch guideline for ECLS treatment, and are experts in the field of ECLS therapy. The project group members are well-positioned to guarantee dissemination of the insights obtained among their colleagues, by presenting the results at national and international podia and by writing reports and papers.

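### The primary question and the foreseen conclusions are superiority-type statements about bleeding and outcome, but the only primary test is non-inferiority of a net composite

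*Protocol article*

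**What the plan says.** **The question.** Objectives {7} asks whether UFH with lower targets, or LMWH, "leads to a reduction in the occurrence of major bleeding without an increase in thromboembolic complications or a negative effect on outcome" relative to usual care. It adds: "We expect fewer complications and improvement of survival after ECMO therapy for both interventions". The Discussion repeats the question.

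**The foreseen conclusions.** Dissemination plans {31a} opens with the condition "If our study indeed shows that reduced anticoagulation targets improve outcomes" and makes implementation follow from it. The last paragraph of the Discussion sets a similar condition, naming fewer bleeding complications as well as better outcome.

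**The test.** Trial design {8} describes a "three-armed, randomized, non-inferiority open-label study" and states: "Allocation is in a 1:1:1 ratio". Under Primary study parameters, an absolute risk reduction with a 95% CI is calculated, and then: "The confidence interval of the risk reduction will be compared with the non-inferiority marge of 7.5% of both intervention arms". Outcomes {12} gives the rationale: "This composite outcome was designed to capture the net clinical effect of reduced anticoagulation targets".

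**Bleeding on its own.** It appears in the secondary list: "7) the individual components of the composite outcome, (8) all thromboembolic complications combined, and (9) all hemorrhagic complications combined". Secondary study parameters plans between-group difference tests for these, adjusted for center and ECMO mode. It states no testing order and no error control.

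**Position on superiority.** The limitations part of the Discussion says that non-inferiority is the aim and superiority is not, because superiority would call for a wider aPTT contrast or many more patients.

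**The concern.** The objective and the test are different hypotheses. The objective claims a reduction in one component (major bleeding) with no increase in another (thromboembolism). The test asks whether the net event rate is less than 7.5 points worse. Because components can offset each other, a pass is compatible with the thromboembolic increase that the objective rules out, and also with no bleeding reduction at all.

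The Discussion pulls both ways: it disclaims superiority and, a few paragraphs later, looks ahead to a conclusion of less bleeding and better outcome. At stake is whether the trial can give an error-controlled answer to its own primary question, and whether a non-inferiority result might later be read as improvement.

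**Working it through.** **Inputs.** Sample size {14} gives 70% (usual care) v 60% (experimental), margin 7.5 points, alpha 5% one-sided (a 90% two-sided CI), power 80%, 91 per group and 330 enrolled, so 330/3 = 110 per arm. Primary study parameters gives a 95% CI. I carry both CI levels.

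**1. The plan's own figure.** Variance term: 0.6×0.4 + 0.7×0.3 = 0.45. Distance from the margin: 0.10 + 0.075 = 0.175. n = 0.45 × (1.645 + 0.842)² / 0.175² = 90.9, so 91 per group. Reproduced.

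**2. What an observed benefit allows.** SE at 110 per arm = sqrt(0.45/110) = 0.0640. Benefit is usual care minus experimental. Non-inferiority needs a benefit above z×SE − 0.075; superiority needs a benefit above z×SE.

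| CI | z×SE | Non-inferiority from | Superiority from |
|---|---|---|---|
| 95% | 1.96×0.0640 = 12.5 points | 5.0 points | 12.5 points |
| 90% | 1.645×0.0640 = 10.5 points | 3.0 points | 10.5 points |

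Between the two limits the result is non-inferiority only. If the trial observes exactly its planned 10 points, the upper limit for excess events is −10 + 12.5 = +2.5 (95% CI) or −10 + 10.5 = +0.5 (90% CI): inside the margin, but not below zero. With 91 per arm the bands are 6.3 to 13.8 and 4.1 to 11.6 points, and still contain 10.

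**3. Offsetting components.** This split is my illustration, not a figure from the article. Suppose bleeding falls by 12 points and thromboembolism rises by 7 in different patients: net 65% v 70%. SE = sqrt((0.65×0.35 + 0.7×0.3)/110) = 0.0631. Upper 95% limit = −5 + 1.96×6.31 = +7.4, just under 7.5. As an observed result this passes, although narrowly.

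**4. Power for composite superiority at 70% v 60%, 110 per arm.** Phi(0.10/0.0640 − 1.96) = 35% (95% CI); Phi(0.10/0.0640 − 1.645) = 47% (90% CI). With pooled variance these are 34% and 46%. For 80% power about 356 per arm are needed at two-sided 5%, or 281 at one-sided 5%.

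**5. Alpha within one comparison.** In 1,000,000 simulated trials at 70% v 70%, 110 per arm, non-inferiority followed by superiority from the same CI was claimed in 2.6% (95% CI) and 5.1% (90% CI), about nominal.

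**6. Where to put bleeding.** If it waits for composite superiority, then at the planned rates it is never reached in 1 − 0.35 = 65% of trials (95% CI). If it waits only for non-inferiority, whose power is Phi(0.175/0.0640 − 1.96) = 78%, it is blocked in 22%. With a 90% CI the corresponding figures are 53% and 14%.

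**7. Power for bleeding.** The Abstract gives bleeding complications as 55%; using that as the control rate of major bleeding is an assumption. At 110 per arm and two-sided 5%, power is 11%, 32%, 61% and 85% for true reductions of 5, 10, 15 and 20 points.

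**The case against.** The strongest reply is that superiority was considered and declined, for a stated reason that the arithmetic supports (about 356 per arm against 110). A superiority step is then a design preference, and testing order is commonly left to an analysis plan that is not shown. This stands to the extent that the absence of such a step is not an error in itself. It does not remove the mismatch, because the objective and the foreseen conclusions are worded in this article and an unseen plan cannot change them.

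Three stronger readings are tempting and are not supported:

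- A reader might infer that bleeding is not tested at all. It is: the components and all hemorrhagic complications are secondary endpoints with adjusted difference tests. What the article does not give is an order or error control tying them to the primary result.
- A reader might infer that the investigators plan to report a non-inferiority pass as improvement. The sentences in Dissemination plans {31a} and the Discussion are conditional and are not decision rules. They do not say which test would satisfy the condition.
- A reader might infer that a superiority step is free in every respect. It costs no alpha only within one experimental-versus-control comparison.

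It is also fair that the 95% CI will be reported anyway, so anyone can see whether it excludes zero. That covers the composite informally. It does not cover bleeding, since composite superiority would support a better net outcome and not less bleeding.

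**Conclusion.** The point holds as an inconsistency between objective, test and foreseen conclusions. The non-inferiority test itself remains valid for what it tests. A pass would not answer the primary question as worded, and the trial's own planned effect falls in the range where non-inferiority is shown and improvement is not: 5.0 to 12.5 points with a 95% CI, 3.0 to 10.5 with a 90% CI.

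These limits rest on the planned event rates, 110 analyzed per arm without drop-outs, and an unadjusted normal approximation. Adjustment for center and ECMO mode would shift them somewhat. The bleeding power figures rest further on the assumed 55% control rate.

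**What to change.** 1. Settle the CI level first: Sample size {14} uses 90% two-sided, Primary study parameters 95%.
2. For each experimental arm against usual care, pre-specify an ordered sequence that starts with non-inferiority on the composite and adds superiority on the composite, read from the same CI. Place the test of major bleeding so that it does not depend on composite superiority. One workable order is non-inferiority, then major bleeding, then composite superiority. If bleeding and composite superiority are instead tested side by side after non-inferiority, they must share alpha, because two tests at full level could raise the error to as much as twice nominal.
3. Report the thromboembolic difference with its CI beside the bleeding result, and limit any statement about no increase to what that CI excludes.
4. State the low power: about 35% for composite superiority with the 95% CI, about 46% with the 90% CI.
5. Handle the two experimental arms and the interim look separately. Two independent comparisons at 5% each give 1 − 0.95² = 9.75%; at 2.5% each, 1 − 0.975² = 4.9%.
6. Reword Objectives {7}, Dissemination plans {31a} and the two Discussion paragraphs so that better outcome is claimed only if composite superiority is met, and less bleeding only if the bleeding test is met. If the sponsor prefers no superiority tests, the rewording alone, in non-inferiority terms, removes the contradiction.

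The cost is a few lines in the protocol and analysis plan and no extra patients. Within one comparison it costs no alpha. The change should be fixed before anyone responsible for the plan sees unblinded results.

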## Trial design {8}

We will perform a multi-center phase 3, three-armed, randomized, non-inferiority open-label study in patients receiving veno-venous (VV) and veno-arterial (VA) ECMO therapy. Allocation is in a 1:1:1 ratio.

## Methods: participants, interventions, and outcomes

### Study setting {9}

This study will be conducted on the intensive care units of over ten Dutch and Belgian ECMO referral centers. A complete list of all participating hospitals can be found on clinicaltrials.gov.

### Eligibility criteria {10}

All adults receiving ECMO treatment at the ICU of one of the participating centers during the study period are eligible for inclusion.

The exclusion criteria are as follows: (1) patients in whom the ECMO is only used to bridge a procedure like a high-risk percutaneous coronary intervention or during surgery; (2) no (deferred) informed consent; (3) vital indication for robust anticoagulation (e.g., mechanic mitral valve, pulmonary embolism, a clot in the cardiac ventricle); and (4) a history of heparin-induced thrombocytopenia (HIT).

### Who will take informed consent? {26a}

The study intervention regards an emergency intervention that has to be applied without delay and fulfills the ethical requirement of clinical equipoise. The study participant can benefit from the intervention, but up to now, there is a state of honest, professional disagreement in the community of expert practitioners as to the preferred treatment. Furthermore, the eligible patients have an extremely high risk of death and the legal representatives will therefore be in a disturbed mental state complicating an immediately informed decision. For the present study, the local investigator or research nurse will inform the patient about the study intervention if and when his consciousness recovers. As the patient usually remains unable to communicate for several days to weeks, the legal representative is contacted as soon as possible and asks for deferred proxy consent for use of the study data. The rationale for the deferred consent procedure is the clinical equipoise of the interventions, the emergency of the intervention, and the possible benefit for the patient with a positive benefit-risk ratio. If the patient has died before deferred consent could reasonably be obtained, the study data will still be used.

### Additional consent provisions for collection and use of participant data and biological specimens {26b}

This trial does not involve collection of biological specimens.

### Interventions

#### Explanation for the choice of comparators {6b}

We hypothesize that lower anticoagulation targets will result in fewer complications and a better outcome for patients receiving ECMO therapy. We have added the LMWH group because this kind of anticoagulation could provide a more stable level of anticoagulation. Moreover, the safety and potential superiority of subcutaneously administered LMWH compared to intravenous UFH have been described for therapeutic anticoagulation in critically ill patients [9]. LMWH is therefore the method of choice for anticoagulation in the ICU and has been demonstrated to be safe in other extracorporeal circuits such as renal replacement therapy and left ventricular assist device (LVAD) [10]. A disadvantage of LMWH may be the monitoring of the level of anticoagulation with anti-fXa levels instead of aPTT, which may be less reliable.

#### Intervention description {11a}

Eligible patients will be randomized in a 1:1:1 ratio between three anticoagulation strategy’s during ECMO therapy: (1) UFH with a target of 2–2.5× baseline aPTT (usual care, about 60–75 s), (2) UFH with a target of 1.5–2.0× (45–60 s), and (3) therapeutic dosage LMWH guided by weight and renal function. Adjustment of heparin and dosage of LMWH will be done according to the local anticoagulation protocols of the participating centers. After the start of ECMO timing of anticoagulation administration will be done according to usual care, so maybe postponed in case of postoperative bleeding for up to 24 hours. No additional invasive procedures are performed in the course of this research. Only laboratory or radiological tests that are part of routine medical treatment will be obtained if relevant.

#### Criteria for discontinuing or modifying allocated interventions {11b}

Crossover to another treatment arm than allocated is allowed based on any of the following: (1) meeting one of the components of the primary outcome, (2) an acquired vital indication for high therapeutic anticoagulation, and (3) additional laboratory results that point towards a strong risk for coagulation disorder or hypercoagulation. Crossover to another treatment than allocated is in principle temporary. The timing of reversion is left to the consideration of the treating physician. The crossover will be mentioned in the case report form (CRF) and the primary and secondary outcome parameters will be measured and mentioned in the CRF after crossover as well.

#### Strategies to improve adherence to interventions {11c}

On-site kick-off meetings are planned before the start of recruitment with the local investigators, research nurses, and treating physicians to explain our hypothesis and the need for this study and will be repeated yearly. By this, we believe the adherence to the study protocol and recruitment overall will be optimal. The monitoring plan will be described at point 23.

#### Relevant concomitant care permitted or prohibited during the trial {11d}

Implementing of three anticoagulation strategy’s during ECMO support will not require alteration to concomitant usual care pathways (including use of any medication) and these will continue for all three trial arms.

#### Provisions for post-trial care {30}

There is no anticipated harm and compensation for trial participation.

